### Study procedure

2.6

Children aged 12 months to 5 years with a confirmed diagnosis of IgE-mediated HEA will be invited to participate in the study. During a medical visit at the department, the recruiting physician will conduct a thorough interview with the parent or guardian, perform a physical examination of the child, review the patient's previous medical records – and perform the eligibility screening.

Children who meet the study eligibility criteria will be randomly assigned to either the intervention or control group. Parents will receive detailed information regarding the study procedure, the upcoming OFC, and the potential benefits and risks of participation. Informed consent will then be obtained from each child's legal guardian, with the form signed in duplicate.

All participating children will begin the introduction of hen's egg proteins into their diet following either the 4-EL (intervention group) or 5-EL (control group). Each subsequent stage of the EL will be initiated with an OFC involving progressively less processed forms of hen's egg proteins: muffin with 0.75 g; muffin with 1.5 g; pancake; hard-boiled egg; soft-boiled egg (Table 2). During the 6-week interval between each stage, parents will introduce the allergen at the previously tolerated dose in the home setting (see Intervention).

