### Eligibility criteria

2.4

Eligibility for study participation requires full compliance with all inclusion and exclusion criteria outlined in Table 1 at the time of enrollment.

**Table 1 T1:** Inclusion and exclusion criteria for pediatric patients with hen's egg allergy.

Inclusion criteria	Exclusion criteria
Age ≥12 months and ≤5 years. Diagnosis of IgE-mediated HEA confirmed according to the EAACI guidelines by a positive OFC with hen's egg proteins. In children with high-risk HEA (e.g., history of anaphylaxis), diagnosis can be based on elevated specific IgE levels to hen's egg proteins and/or individual egg components and/or positive skin tests^a^. On a therapeutic elimination diet for at least 6 months, measured from the last allergic reaction to egg (in accordance with BSACI guidelines) (16). Eligible regardless of the risk of systemic reactions (e.g., anaphylaxis) or asthma. Good general health Written informed consent signed by the child's guardians. Demonstrated good cooperation from the patient's guardians.	Confirmed wheat allergy and/or celiac disease. Uncontrolled asthma, defined as the presence of shortness of breath, cough, chest tightness, or auscultatory changes despite treatment. Signs of exacerbation of a chronic disease. Signs of acute infectious disease (e.g., acute rhinitis, cough, subfebrile or febrile states). Exacerbation of another allergic disease (e.g., conjunctivitis, allergic rhinitis, atopic dermatitis). Anaphylaxis due to hen's egg proteins within the last 6 months. Use of antihistamines within 3–10 days before the challenge^b^ (depending on the drug and indication; time-limited contradiction – relative exclusion criterion). Acquired tolerance to baked hen's egg proteins or advancement to a higher step of the egg ladder. Use of immunosuppressive drugs or immunotherapy.

BSACI, British Society for Allergy and Clinical Immunology; EAACI, European Academy of Allergy and Clinical Immunology; HEA, Hen's egg allergy; HEPs, Hen's egg proteins; OFC, oral food challenge.

a Exceptions to the oral food challenge (OFC) protocol may be made for patients presenting with severe anaphylaxis or significantly elevated specific IgE levels (3.5 KU/L) to egg white proteins (designated as a high-risk challenge, where standard protocols contraindicate OFC due to anaphylaxis risk) (7, 21, 22).

b Temporal constraint (relative exclusion criterion).

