### Sequence generation and allocation concealment

2.16

Children will be randomised to either the intervention or control group immediately after enrolment. An independent investigator with no clinical involvement in the trial will generate random assignments using a computer-generated random number table. The random number will be generated in blocked randomization (using the block of 2) with a 1:1 allocation ratio. The randomization will be created using StatsDirect statistical software (Stats-Direct statistical software; http://www.statsdirect.com; England: StatsDirect, 2024).

Allocation concealment will be ensured through the use of opaque, sealed and numbered envelopes. The data regarding intervention assignments will be stored in a sealed envelope in a secure location within the administrative part of the department. An independent person will open the next consecutively numbered envelope and provide the allocation information to the study physician.

Since this is an open-label trial, both the participants and the study team will be aware of the treatment allocation on randomization. In the event of any medical issues, the assigned treatment information will already be accessible to the study physicians and principal researcher, eliminating the need for code-breaking procedures.

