## Discussion

3

Currently, there are no standardized protocols for the assessment of tolerance acquisition using the EL approach. Furthermore, scientific evidence supporting the efficacy and safety of the EL in children with HEA remains limited. According to the BSACI guidelines, reintroduction of baked egg as an ingredient may be performed in children aged 12 months or 6 months from the last reaction (15). Additionally, regular ingestion of baked egg may accelerate the acquisition of tolerance to unheated egg and reduce dietary exclusions.

This study will assess the efficacy of the 4-EL compared to the 5-EL in children with confirmed IgE-mediated HEA. Due to limited evidence, high-quality trials are needed. However, no study is perfect, and this trial also has some limitations. The risk of bias is associated with the lack of blinding, which is not feasibility due to the nature of the intervention. Although participant will receive the intervention in both study arms (the 4-EL or 5-EL), some parents may prefer a different ladder than the one assigned (i.e., the shorter arm may be associated with fewer hospital visits). A second limitation is the home preparation of tested foods by caregivers. Although standardized recipes will be provided, a risk of inaccurate food preparation or modification cannot be excluded. To minimize this bias, caregivers will be asked before each challenge, whether any modifications were made, and the total amount and portion of the prepared foods will be weighed. Another limitation is the absence of a formal sample size calculation and the pilot nature of this trial. Due to limited evidence, the sample size was only estimated. However, it is considered sufficient to detect a clinical difference between these two egg ladders and to inform further confirmatory trials.

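### Section 2.6 places random assignment before parental information and consent, contradicting Table 1 and section 2.16

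*Protocol article*

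**What the plan says.** Three parts of the protocol article bear on when consent is taken relative to allocation.

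- **Section 2.6 (Study procedure)**, after describing the screening visit, states: "Children who meet the study eligibility criteria will be randomly assigned to either the intervention or control group". The next sentence is: "Parents will receive detailed information regarding the study procedure, the upcoming OFC, and the potential benefits and risks of participation". The one after that begins: "Informed consent will then be obtained from each" child's legal guardian.
- **Section 2.4 (Eligibility criteria)** states: "Eligibility for study participation requires full compliance with all inclusion and exclusion criteria outlined in Table 1 at the time of enrollment". Among the inclusion criteria, Table 1 lists: "Written informed consent signed by the" child's guardians.
- **Section 2.16 (Sequence generation and allocation concealment)** states: "Children will be randomised to either the intervention or control group immediately after enrolment". It adds that families and study team learn the allocation at randomisation.

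Two other places matter for the consequences. Section 2.19 promises an ITT analysis of every randomised child, whatever happens afterwards. The Discussion, listing limitations of an unblinded trial, accepts that "some parents may prefer a different ladder than the one assigned" and gives fewer hospital visits in the shorter arm as the example.

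**The concern.** Section 2.6 sets out the recruiting visit step by step, so it is the section that site staff are most likely to work from. In its order, a child has an arm before the guardians have been fully informed or have signed.

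Three things would be at stake if that order were followed.

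- **Consent.** Children would be assigned to an arm of a trial of supervised allergen challenges before their guardians agreed to take part.
- **Concealment.** Sealed envelopes protect the decision to enter the trial from knowledge of the next allocation. If parents decide after the envelope is opened, that protection is lost for their decision.
- **Analysis set.** A child whose parents refuse after allocation has been randomised but has no consented data. Leaving the child out departs from the promised ITT analysis. Keeping the child in means imputing an outcome with little or nothing to impute from. Section 2.13 on premature withdrawal does not help, because its rule for documenting endpoints stops where parents refuse further participation.

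The arms differ in ways that parents can see: four challenges over 18 weeks against five over 24, and a first muffin with 1.5 g against 0.75 g of egg protein. Refusal that depends on the arm is therefore possible, though the article does not predict it.

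**Working it through.** **1. The order of steps, side by side**

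| Step | Section 2.6 as printed | Sections 2.4 and 2.16 together |
|---|---|---|
| 1 | Eligibility screening | Screening against Table 1 |
| 2 | Random assignment | Signed consent (a Table 1 criterion, met at enrolment) |
| 3 | Information to parents | Enrolment |
| 4 | Consent | Randomisation |

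Section 2.6 is also inconsistent within itself when read with Table 1. It randomises children who meet the eligibility criteria, and those criteria already include signed consent, yet it obtains consent two sentences later. No other section states that consent is signed before the envelope is opened, and none says how a refusal after allocation is handled.

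**2. The plan's own figure**

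Section 2.9 recruits 94 children (47 per arm) so that 84 (42 per arm) complete after 10% dropout: 42 / (1 − 0.10) = 46.7, rounded up to 47, and 2 × 47 = 94. The figure reproduces. Moving consent ahead of randomisation changes no figure in the article.

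**3. Illustration of what post-allocation refusal could do**

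Inputs:
- 47 children randomised per arm (section 2.9).
- p = 0.69, tolerance rate in both arms. This is the pooled literature rate in the Introduction, used here as an assumption.
- r = share of one arm refusing after allocation. The article gives none; 10% and 20% are assumed.
- q = the rate that refusers would have had. Not given; 0.30 to 0.90 is assumed.

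If refusers are dropped, the observed rate in that arm is (p − r·q) / (1 − r).

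| r | q | Observed rate | Shift (points) |
|---|---|---|---|
| 10% | 0.30 | (0.69 − 0.03) / 0.90 = 73.3% | +4.3 |
| 10% | 0.69 | 69.0% | 0 |
| 10% | 0.90 | (0.69 − 0.09) / 0.90 = 66.7% | −2.3 |
| 20% | 0.30 | (0.69 − 0.06) / 0.80 = 78.75% | +9.75 |
| 20% | 0.69 | 69.0% | 0 |
| 20% | 0.90 | (0.69 − 0.18) / 0.80 = 63.75% | −5.25 |

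If refusers are instead kept and counted as failures, the shift is −r·p: −6.9 points at 10% and −13.8 points at 20%.

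**4. Effect on completers**

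If the full 10% dropout also occurs among those who stay, completers in the affected arm number 47 × 0.90 × 0.90 = 38.1 at 10% refusal and 47 × 0.80 × 0.90 = 33.8 at 20%, against the target of 42. If refusals replaced the planned dropout, 10% refusal (4.7 children) would leave 42.3, which still meets the target.

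**The case against.** The best defence is that 2.6 is a loosely ordered narrative. The randomisation sentence carries no time marker, and the one sequencing word follows the information sentence, so it can be read as inform first, then obtain consent. The randomisation sentence covers only eligible children, and under Table 1 a child without signed consent is not eligible. Section 2.16, which governs allocation, puts enrolment first. Consent before randomisation may well be what was intended.

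Much of this stands. A reader might infer from 2.6 that the trial has chosen to randomise without consent; sections 2.4 and 2.16 point the other way, so the documents do not support that. The argument does not remove the contradiction, however. It identifies 2.6 as the section to correct.

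The defence is also right on the consequences. A reader might infer that refusals will differ by arm, or that the ITT analysis cannot be done. Both hold only if sites follow 2.6 and some parents then refuse. The Discussion speaks of parents preferring a ladder, not of refusing consent. Preference would remain with consent taken first, because sections 2.6.1 and 2.13 allow withdrawal at any stage. What the correct order adds is that such a child has consented and clearly belongs in the ITT set; it does not prevent loss of outcome data driven by preference.

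Finally, a reader might infer a bias in one particular direction, for instance by supposing that refusers are the children with the better prognosis. Nothing in the article links a wish for fewer visits to the chance of tolerance, and if refusers resemble the rest the shift from dropping them is zero.

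**Conclusion.** The point holds as an internal contradiction: 2.6 lists allocation before information and consent, whereas Table 1 and 2.16 require consent first. This needs no numerical assumption.

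The harm is conditional on sites following 2.6 and on some parents refusing once they know the arm. In that case entry to the trial is no longer protected from knowledge of the allocation, and the ITT set of all randomised children contains some without consented data. The size and sign of any bias cannot be determined from the article. The ranges for dropped refusers, about +4.3 to −2.3 points at 10% refusal and +9.75 to −5.25 at 20%, rest on three assumptions: refusal confined to one arm, 69% tolerance in both arms, and 30% to 90% tolerance among refusers. They show that the effect need not be negligible; they do not estimate it.

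This is more than a clerical matter, because one paragraph touches consent, concealment and the analysis set together, and a child already randomised in the wrong order cannot be put right afterwards.

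**What to change.** Rewrite the paragraph in 2.6 in one order that agrees with 2.4 and 2.16: eligibility screening, full information on both ladders, signed consent, then opening of the next numbered envelope. State that a child counts as randomised once the envelope is opened after consent, and that every such child is included in the ITT analysis, including any whose parents withdraw on learning the arm.

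Section 2.3 schedules recruitment from July 2025, so the sites should also confirm for any child already enrolled that the consent form was signed before the envelope was opened, and report any case where it was not.

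The cost is wording in the protocol and site instructions, plus that one check of records. It needs no extra visit or participants, and the sample size figures do not change. A reader might infer that baseline questionnaires must also be completed before the envelope is opened; that does not follow from this contradiction and is not part of the correction.

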#### Parental education on allergen introduction in the home setting

2.6.1

The study products should be administered at home, preferably the early afternoon, after the child returns from daycare, to allow for optimal monitoring of any delayed reactions. Parents will be encouraged to keep a minimum interval of 2 h between servings. If the allergen is not administered for more than a week, the interval between subsequent OFCs should be extended proportionally to the length of the break.

The study product must not be administered on an empty stomach. In the presence of acute infectious symptoms, administration of the scheduled portion of hen's egg proteins should be postponed for at least three days or until symptoms resolve and child is back to baseline, because as a cofactor it may affect the child's tolerance to ingested allergens (23).

Throughout the intervention phase, a strict elimination of hen's egg proteins outside the prescribed product must be maintained. The use of commercially available food products containing hen's egg proteins – including those listing them as ingredients or potentially containing trace amounts – is not recommended due to the unknown hen's egg proteins content, in order to prevent unintentional cumulative allergen exposure.

To ensure participant safety, all parents will receive both verbal and written information concerning the potential for adverse reactions, including anaphylaxis, during home-based allergen administration. This will be accompanied by detailed management protocols. Prior to initiating the home introduction of the study food, study personnel will verify that all required emergency medications are available, as specified in the adverse event protocol. In addition, parents and caregivers will undergo comprehensive training on the recognition and appropriate management of allergic reactions.

Furthermore, parents are encouraged to contact the research team for guidance if any difficulties arise during progression through the egg ladder. It is emphasized that withdrawal of consent at any stage of the study will in no way affect the child's continued medical care or access to appropriate treatment.

#### Assessments

2.6.2

Anthropometric data for the child, specifically height and weight, will be collected at study enrollment and at the end of the observation period (either at 18 or 24 weeks, depending on the assigned study arm). Weight (in kilograms) and standing height (in centimeters) will be measured according to standardized protocols.

Prior to the initial OFC and following completion of the egg ladder, the subjective quality of life of all enrolled children and their caregivers will be assessed using the validated, allergy-specific Parent Form of the Food Allergy Quality of Life Questionnaire (FAQLQ-PF) (24). The FAQLQ-PF was developed to measure parental perceptions of health-related quality of life in children aged 0–12 years with food allergies and includes three domains: emotional impact, food anxiety, and social and dietary limitations. In this study, only the age-appropriate versions of the questionnaire for children under 4 years and for those aged 4–6 years will be used, in accordance with the inclusion criteria. These versions contain 14 and 26 items, respectively. A total score ranging from 0 to 6 is calculated as the mean of the subscale scores.

Prior to each OFC, caregivers will assess their level of anxiety specifically related to the OFC using the Subjective Units of Distress Scale (SUDS) (25). On this scale, parents will rate their anxiety from 1 to 100, where 0 represents no anxiety or complete relaxation, and 100 represents extreme anxiety – the highest level of distress ever experienced.

In children with atopic dermatitis, objective skin lesions will be evaluated using the objective SCORAD index (oSCORAD) (26), a validated variant of the Severity Scoring of Atopic Dermatitis (SCORAD). Assessment will be performed prior to the initial OFC and during follow-up examinations at the end of each observation period.

The SCORAD index is a key tool for evaluating the severity of atopic dermatitis and monitoring treatment response It includes both objective measures (extent and intensity of skin lesions), and subjective symptoms (pruritus and sleep disturbance) reported over the preceding 72 h. The oSCORAD omits the subjective component, focusing exclusively on objective clinical findings. The maximum oSCORAD score is 83, with an optional addition of up to 10 points for disfiguring or function-limiting changes in severe cases. Severity categories are defined as follows: mild (<15), moderate (15–40), and severe (>40).

All children who experience anaphylaxis during the study period (either over 18 or 24 weeks, depending on the assigned study arm) will be assessed using the updated 2023 World Allergy Organization (WAO) clinical criteria for anaphylaxis (27). This scale categorizes allergic reactions during allergen exposure into five grades, with anaphylaxis defined as reactions falling within grades 3–5.

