### Study objective and hypothesis

2.1

The primary aim of this study is to evaluate and compare the efficacy and safety of a 4-step egg ladder (4-EL) and a 5-step egg ladder (5-EL) in children diagnosed with IgE-mediated hen's egg protein allergy.

We hypothesize that the 4-EL, with 6-week intervals, will be sufficient for assessing tolerance to hen's egg proteins in children with IgE-mediated allergy and will result in a greater proportion of children achieving tolerance to raw egg white, confirmed by OFC, compared to the 5-EL, with the same timeframe. This corresponds to an 18-week tolerance acquisition period in the 4-EL group vs. 24 weeks in the 5-EL group.

There is some evidence suggesting that the introduction of baked egg in high-risk children (e.g., those with a history of anaphylaxis) may be both safe and effective (21). However, it remains unclear whether the initial tested dose of baked hen's egg protein in such cases should be lower than, or the same as, that recommended for the general pediatric HEA population.

Therefore, we decided to compare two ladder protocols: the 4-EL, beginning with a muffin containing 1.5 g of hen's egg proteins, and the 5-EL, in which the first two steps consist of muffins containing 0.75 g and 1.5 g of egg proteins, respectively. This approach allows for a reduced allergen load at initial exposure and a longer cumulative exposure to baked hen's egg proteins. Such a strategy may be more appropriate for specific subgroups of patients, particularly those considered to be at higher risk (21).

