### Sample size justification

2.9

This study is designed as a randomized controlled trial (RCT) to compare the clinical effectiveness and safety of two versions of an egg ladder protocol: one with four steps and the other with five steps, in children with IgE-mediated hen's egg allergy.

A formal sample size calculation based on statistical power was not feasible due to the lack of standardized data regarding allergen content and clinical reactivity across different baked egg preparations used in oral food challenges. As noted in the existing literature, studies assessing the immunological and clinical progression through the egg ladder remain limited, and standardized endpoints have not yet been universally defined.

Therefore, this trial was informed by available clinical evidence and precedent from similar studies involving the milk ladder in cow's milk-allergic children. In particular, a comparable RCT evaluating the impact of introducing baked cow's milk on tolerance development included 84 children (42 per arm) and demonstrated sufficient power to detect clinically meaningful differences (14).

Moreover, a recent randomized trial by De Vlieger et al. (12), which evaluated short- vs. long-term guided gradual egg reintroduction in baked egg–tolerant children, also enrolled 78 children (39 per arm) and successfully identified significant differences in tolerance acquisition timelines.

Based on this evidence and our clinical experience, a total of 94 children (47 per group) will be recruited to allow for an anticipated 10% dropout rate, ensuring that at least 84 participants (42 per group) complete the trial. This sample size is considered both feasible and appropriate to meet the study objectives while allowing an initial exploration of clinical differences between the two egg ladder variants. This pilot trial will generate effect size estimates to inform future confirmatory studies and formal sample size calculations.

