○grade 1: includes nausea and/or mild abdominal pain without altered activity;○grade 2: persisting (≥20 min) and non-distractable abdominal pain and/or vomiting (not due to gag or taste aversion) and/or diarrhea;○grade 3: severe, persistent (≥20 min), intractable abdominal pain and/or vomiting (excluding retching or taste aversion) and/or diarrhea, assessed during each OFC measured during the observation period (18 or 24 weeks, depending on the study arm).In the subgroup of children with AD, changes in the total score of the oSCORAD index (26) will be assessed before and after each OFC. Any documented exacerbation of AD symptoms following OFC will be also recorded.Change in age-adjusted *z*-scores for weight and length/height, evaluated using the WHO growth charts (31), from baseline (prior to the first OFC) to the end of the observation period (18 or 24 weeks, depending on the study arm).Change in the total score of the FAQLQ-PF (24), at the end of the observation period (18 weeks and 24 weeks, depending on the study arm) from baseline.Mean difference in caregiver anxiety levels, measured by the Subjective Units of Distress Scale (SUDS) (25) prior to each OFC, between study groups at each time point.The proportion of children with full adherence to the intervention protocol, defined as consumption of at least one portion of a tolerated hen's egg proteins dose three times during last week of break in period, in the same form and quantity as tested during the OFC. Data will be collected through the Egg Ladder Monitoring Diary and assessed throughout each break in period (between the following steps of each ladder).

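### Stature is to be measured standing at every age from 12 months, while the growth outcome is a length/height z-score; Sections 2.6.2 and 2.11.2 need to be reconciled

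*Protocol article*

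**What the plan says.** Section 2.6.2 of the protocol article (Assessments) limits anthropometry to two variables at two time points: "specifically height and weight, will be collected at study enrollment and at the end of the observation period". It then names the method: "standing height (in centimeters) will be measured according to standardized protocols". Recumbent length is not mentioned, and no age is given at which the method would change.

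Section 2.11.2 (Secondary outcomes) defines the growth outcome as the change from baseline in age-adjusted z-scores "for weight and length/height, evaluated using the WHO growth charts".

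Table 1 in Section 2.4 sets the entry age: "Age ≥12 months and ≤5 years". Section 2.6 repeats the 12-month lower limit.

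The interval between the two measurements differs by arm. Section 2.1 puts it this way: "This corresponds to an 18-week tolerance acquisition period in the 4-EL group vs. 24 weeks in the 5-EL group".

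**The concern.** The outcome definition provides for length in some children, but the measurement section provides only for standing height. Staff who follow Section 2.6.2 to the letter would stand a 12-month-old, an age at which a standing measurement is often unreliable.

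A standing value is normally a little shorter than a recumbent one. If it is scored against a reference built on length, the z-score comes out too low. If the reference then changes from length to height between the two visits, the child appears to gain stature when only the reference has changed.

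Because the outcome is a within-child change over 18 or 24 weeks, a mismatch at one visit only goes straight into the change score. The longer 5-EL interval also means that slightly more children in that arm would pass the switch age.

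**Working it through.** The article gives no SD, expected change or power for the growth outcome, so there is no stated figure to reproduce. The check has two parts.

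**1. Sections side by side.** Section 2.6.2 specifies standing height, Section 2.11.2 specifies length/height, and Section 2.4 admits children from 12 months. No sentence links the first two by age, position or conversion.

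**2. Size, if standing height is scored uncorrected.**

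Inputs from the article:
- entry from 12 months to 5 years (Section 2.4)
- intervals of 18 and 24 weeks (Section 2.1)
- 42 completers planned per arm (Section 2.9)

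Assumptions, not in the article:
- length exceeds standing height by 0.5 to 1.0 cm (central 0.7)
- the reference SD is 2.5 to 3.5 cm (central 3.0)
- the chart switches from length to height at 24 months
- no correction is applied
- entry ages are uniform over 12 to 60 months

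*Error in a single z-score* = offset / SD.
- Smallest: 0.5/3.5 = 0.14
- Central: 0.7/3.0 = 0.23
- Largest: 1.0/2.5 = 0.40

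*Share under 24 months at entry* = (24 − 12)/(60 − 12) = 12/48 = 25%.

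*Interval in months* (30.4375 days per month):
- 18 × 7/30.4375 = 4.14
- 24 × 7/30.4375 = 5.52

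*Share turning 2 between visits* = interval / age span.
- 4-EL: 4.14/48 = 8.6%, or 0.086 × 42 = 3.6 children
- 5-EL: 5.52/48 = 11.5%, or 0.115 × 42 = 4.8 children

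Children under 24 months at both visits carry nearly the same offset twice, so it largely cancels in their change score. Only those who cross the switch age show the spurious gain.

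*Mean upward bias in change*, central case:
- 4-EL: 0.0862 × 0.233 = 0.020 z
- 5-EL: 0.1150 × 0.233 = 0.027 z

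*Between-arm bias* = (0.1150 − 0.0862) × error.
- Central: 0.0288 × 0.233 = 0.007 z
- Range: 0.0288 × 0.143 = 0.004 to 0.0288 × 0.40 = 0.012 z

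*Added SD of the change score* = error × √[p(1 − p)], where p is the share crossing.
- 5-EL, central: 0.233 × √(0.115 × 0.885) = 0.07 z
- 5-EL, largest: 0.40 × √(0.115 × 0.885) = 0.13 z

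*Sensitivity to age mix.*
- Entry only at 12 to 36 months: the shares crossing are 4.14/24 = 17% and 5.52/24 = 23%. The between-arm bias is 0.0575 × 0.233 = 0.013 z (range 0.008 to 0.023).
- Upper age limit read as up to 72 months: the shares fall to 4.14/60 = 6.9% and 5.52/60 = 9.2%.

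**The case against.** The best defence is that the article leaves room for the right practice. Section 2.6.2 refers to standard measuring procedures and Section 2.11.2 names length as well as height, so the two can be read together as length in the youngest children. Position and z-score conversion are also details that an article often leaves to the full protocol or a measurement manual.

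Part of this stands. A reader might infer that the z-scores of the youngest children are wrong and that change scores will jump at the second birthday. The article does not support that as fact. It requires standing height actually to be taken in children under 24 months, scored against a length reference, and left uncorrected. The article states neither the structure of the chart nor whether a conversion will be used. Nor does it give an expected growth change against which an artefact of this size could be called large.

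A reader might also infer a material imbalance between arms from the unequal intervals. The arithmetic does not show one. The counts of children crossing the switch age are, moreover, upper limits. Under Section 2.5.3 children with a positive challenge leave the study, so some may have no final measurement.

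The condensation argument does not remove the point. The article is not silent on method: it names a position, and that position does not fit part of the enrolled age range or the outcome's own wording. The reference to standard procedures governs how standing height is taken; it does not turn it into length.

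**Conclusion.** The point holds as an inconsistency between Sections 2.6.2 and 2.11.2, with a conditional and small consequence. If standing height is scored uncorrected against a length reference that switches at 24 months, z-scores in children below that age would be about 0.14 to 0.40 too low. About 9% of 4-EL and 11 to 12% of 5-EL children would show a spurious gain of that size. The between-arm bias would be about 0.01 z, and up to about 0.02 with entry at 12 to 36 months.

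The offset, the SD, the switch age, the absence of a correction and the age distribution are all assumptions. The damage is mainly error in individual z-scores and avoidable noise in one secondary outcome. The primary outcome and the sample size are not affected. This is a minor correction, worth making because it is cheap and because the measuring position cannot be recovered later if nobody records it.

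**What to change.** Amend Section 2.6.2 so that recumbent length is measured in children below the growth standard's length-to-height switch (taken here as 24 months, to be confirmed against the standard) and standing height from that age on. Record the position on the CRF at each visit. Where position and chart do not match, apply the standard's own length-height conversion before computing the z-score, with the same rule at both visits.

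With this in place the artefact described above disappears. The cost is a short amendment to Section 2.6.2 and one CRF field. It needs a length board at each of the three departments named in Section 2.3, which paediatric departments can be expected to have. No extra visit or staff is needed.
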